#### Phone-Based Follow-Up Survey

The extent to which physical invitation cards were distributed to invitees will be ascertained through self-reports from inviters during a phone-based follow-up survey after 30 days.

#### Assessment of Primary Outcome

The primary outcome measure is counselor-documented uptake of HIV testing by invitees within 30 days of the enrollment of the inviter. All clients presenting for HIV testing will be asked if they received an HIV testing invitation by SMS text message or a physical invitation card. Counselors will document referral codes from SMS text messages and collect invitation cards. Referral codes will be validated against a database of referral codes issued. A match is interpreted as an invitee presenting for HIV testing.

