**Figure 2 figure2:**
[figure not shown]
The design of the 2-arm randomized controlled trial (RCT). This RCT with 600 adult inviters will be conducted in Moshi, Tanzania. The primary outcome of interest is the uptake of HIV testing among invitees, defined as the number of invitees testing for HIV within 30 days of enrollment of the inviter per 100 inviters. While not all process elements can be observed, the RCT results yield an unbiased estimate of the efficacy of the Confidential Social Network Referrals for HIV Testing (CONSORT) for the primary outcome: inducing additional persons to test for HIV relative to physical invitation cards alone.

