### Primary Outcome

The primary outcome is counselor-documented uptake of HIV testing among invitees within 30 days of the enrollment of the inviter. For invitees who present for HIV testing (invitee testers) after a CONSORT invitation, referral codes, alphanumerical codes that are unique to the phone number of the invitee, will be documented by counselors in logbooks; for invitees presenting with physical invitation cards, counselors will collect the invitation cards.

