#### Social Network–Based HIV Testing Invitations

The enrollment survey will include a survey of inviters’ preferences for extending HIV testing invitations within their social networks. Participants will be asked to think of social network contacts across multiple network dimensions, including partners, family members, friends, coworkers, and other people who are aged 18 years or older and who would benefit from HIV testing. Participants will be asked to whom they would prefer to extend an HIV testing invitation through a physical invitation card; arm 1 participants will also be able to select CONSORT invitations. At the end of the survey, inviters will be given the respective number of coded invitation cards, and arm 1 inviters will be able to send CONSORT invitations to their network contacts (Figure 1).

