### Limitations and Considerations

This study is subject to several limitations and considerations.

First, feasibility considerations limit the study area to include only HCT facilities in Moshi municipality. Invitees may test outside the study area and may thus not be captured by our study. Furthermore, while referral codes and coded invitation cards collected from participating HCT providers offer definitive evidence of a completed HIV test, participants may test without disclosing receipt of CONSORT messages or invitation cards.

Second, the estimated effect sizes are not generalizable to other index populations, other areas in Tanzania, or other parts of Africa. While high mobile phone use rates and stable cellular network coverage suggest good technical feasibility of CONSORT, illiteracy, lack of trust in confidentiality assurances, and stigma remain potential challenges. In the formative work and the pilot study, we will explore options such as computer-assisted self-interviewing for capturing referral information, incentives, and system-level adjustments to maximize acceptability and efficacy.

Third, SMS text messages must be short and concise, can only contain text, and are not encrypted in transit. As implemented in this study, messages are presented as 1-way communication (although a phone number is provided if the invitee has questions). If successful, future work will explore the use of alternative communication options that allow for the secure transfer of audiovisual information and a more interactive experience (eg, through chatbots).

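### The primary outcome is measured by code and card matches rather than distinct persons tested: an SMS-plus-card pair can count twice in arm 1 only, and a code keyed to a phone number need not identify one inviter

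*Protocol article*

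**What the plan says.** The Figure 2 caption sets the outcome in persons: it is "defined as the number of invitees testing for HIV within 30 days of enrollment of the inviter per 100 inviters", and the effect of interest is "inducing additional persons to test for HIV relative to physical invitation cards alone". Analysis of the Primary Outcome models the count at the level of the inviter.

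Assessment of Primary Outcome describes how that count is obtained. "Counselors will document referral codes from SMS text messages and collect invitation cards". Then "Referral codes will be validated against a database of referral codes issued", and "A match is interpreted as an invitee presenting for HIV testing". The section does not say what happens when one client produces more than one match.

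Primary Outcome describes the SMS codes as "alphanumerical codes that are unique to the phone number of the invitee". Design of the RCT opens SMS invitations and cards to arm 1 for any contact and restricts arm 2 to cards. Social Network–Based HIV Testing Invitations first asks all inviters whom they would give a card, and adds that "arm 1 participants will also be able to select CONSORT invitations". Neither section says that a contact may receive only one type.

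Limitations and Considerations discusses undercounting only: testing outside the area, and testing without disclosing an invitation.

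**The concern.** The quantity wanted is persons; the quantity recorded is items handed over. The two agree only if each tester presents exactly one item. Every client is asked about both invitation types, so a client holding both is likely to show both.

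A card-only arm cannot generate an SMS-plus-card pair from one inviter, and the SMS arm can. This part of the miscount therefore does not cancel between arms: it adds to arm 1 and appears as a CONSORT effect.

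The second issue is attribution. The dependent variable is a count per inviter, and the 30-day window starts at that inviter's enrollment. A code tied to a phone number carries the inviter's identity only if no other inviter names that number, or if the system issues a fresh code each time. Overlap is foreseeable, because recruitment is consecutive at facilities in one town and invitee testers may become inviters themselves. SMS codes arise only in arm 1, so this ambiguity does not move a tester between arms. It can change which inviter is credited and whether the test falls inside the window. A client holding an arm 1 SMS and an arm 2 card is a cross-arm case, also without a stated rule.

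**Working it through.** **Inputs.** Statistical Power supplies scenarios of 20, 40, 60, 80 or 100 arm 2 testers and treats the count as Poisson. Assignment to Study Arms expects roughly equal arms, so counts can be compared directly. The share *d* of arm 1 testers who hand in both items is not given anywhere; 5% to 30% is assumed.

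**The plan's own scale.** Statistical Power lists detectable differences of 7, 10, 13, 15, 16 (90% power) and 6, 8, 10, 11, 13 (80% power). They do not reproduce as power figures. At 60 testers and 90% power, a two-sample Poisson comparison at the 5% level needs 36.6 (one-sided) or 41.1 (two-sided), against 13 stated. The listed values equal z × √N with z = 1.645 and 1.282: at N = 60 these give 12.7 and 9.9, which round to 13 and 10. They are half-widths of 90% and 80% intervals for a single count, so they are not used here to judge size.

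**Double counting with no true effect.** Let N persons test in each arm. Then:

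- expected arm 1 matches = N × (1 + d)
- expected arm 2 matches = N, leaving aside duplicate cards, which either arm can have
- spurious rate ratio = 1 + d

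The false-positive rates below come from 400,000 simulated Poisson draws per row and scenario, using z = (x1 − x2)/√(x1 + x2) with a two-sided limit of 1.96.

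| Assumed d | Arm 1 matches at N = 60 | Rate ratio | False positives, N = 20 | N = 60 | N = 100 |
|---|---|---|---|---|---|
| 0% | 60 | 1.00 | 0.050 | 0.049 | 0.050 |
| 5% | 63 | 1.05 | 0.057 | 0.064 | 0.070 |
| 10% | 66 | 1.10 | 0.069 | 0.093 | 0.117 |
| 20% | 72 | 1.20 | 0.110 | 0.198 | 0.286 |
| 30% | 78 | 1.30 | 0.165 | 0.346 | 0.505 |

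**Check by hand, N = 60, d = 20%.** The mean difference is 60 × 0.20 = 12. Each arm 1 tester contributes 1 or 2 matches, so the arm 1 variance is N(1 + 3d) = 96, and the variance of the difference is 96 + 60 = 156 (SD 12.49). The rejection limit is about 1.96 × √(72 + 60) = 22.5. The upper tail is P(Z > (22.5 − 12)/12.49) = P(Z > 0.84) ≈ 0.20, which agrees with the simulation.

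The planned model is zero-inflated negative binomial. Overdispersion would widen the standard errors and lower these false-positive rates, but it would not remove the spurious ratio 1 + d.

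**Attribution.** No frequency is given for several inviters naming one number, so this part is a matter of reading. Primary Outcome ties uniqueness to the phone number, while the model and the 30-day window need an inviter. The CONSORT Intervention section has a unique code going to each invitee number and does not say whether a second inviter's invitation to that number gets a new code.

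**The case against.** The strongest reply is that the matching sentence only says how an invitee is recognized; it does not say that two matches from one client are two invitees. The outcome is defined in invitees, and a full protocol or SAP could hold a deduplication rule. The design also leans towards one type per contact: cards are called a substitute, and the two types are joined by the word or. This lowers the likely frequency. It does not settle the matter, because the article states a counting rule, permits both types and gives no exclusion.

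Several stronger readings are tempting and are not supported:

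- *A shared phone's code cannot be assigned to any inviter.* If two contacts of one inviter share a phone, the code still points to that inviter. The problem needs several inviters naming one number and a reused code. The database of issued codes may also record the inviter.
- *Duplicates can never be removed.* The aggregate abstraction is described under secondary outcomes and covers tester characteristics and test results. The primary outcome rests on logbooks with individual codes and on coded cards, and paper documents are scanned. What can be said is that no client-level link is described.
- *All double counting favors CONSORT.* Duplicate cards can arise in either arm. Only the SMS-plus-card route from a single inviter is specific to arm 1.
- *Presenting and testing are contradictory outcomes.* Limitations and Considerations says codes and cards "offer definitive evidence of a completed HIV test", whereas the assessment rule speaks of presenting. This is mostly wording, and no difference between arms is shown.
- *The spurious gain is close to the detectable difference.* The stated differences are not power figures and make a poor yardstick.

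**Conclusion.** The concern holds in a limited form. The stated rule equates a match with an invitee, arm 1 alone allows one inviter to give one contact both an SMS and a card, and the article describes neither a one-person-one-count rule nor a client-level link. A code keyed to the phone number also leaves the inviter and the 30-day window undetermined when several inviters name the same number and the code is reused.

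The size is unknown. Under the assumed 5% to 30% dual presentation, with 60 true testers per arm and no true effect, arm 1 shows 3 to 18 extra testers and the false-positive rate is about 0.06 to 0.35 in a simple Poisson comparison. If few clients present both items, the effect is small. The case for acting is that the direction of this component is known and that the correction is simplest before data collection.

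**What to change.** 1. Issue codes per inviter-invitee invitation, for SMS and cards alike, so that every item identifies one inviter and one 30-day window.
2. Have counselors complete one line per client, listing every code and card presented and whether a test was done.
3. Define the primary outcome as distinct persons tested, counted at most once per inviter.
4. Prespecify one rule for clients holding invitations from several inviters, including inviters in different arms, with a sensitivity analysis under an alternative rule. Crediting the earliest valid invitation, with crediting all as the alternative, is one workable choice.

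The cost is a small change to code generation in mParis and to the logbook, and possibly a smaller arm 1 count.

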#### Assessment of Secondary Outcomes

The acceptability of CONSORT among inviters will be described by the percentage of inviters extending at least 1 CONSORT invitation and the average number of CONSORT invitees per inviter. This outcome is assessed only for arm 1 participants.

For invitee testers, basic sociodemographic and risk characteristics (age, gender, marital status, pregnancy status, and previous testing), as well as their HIV test result, will be abstracted in aggregate form from administrative data collected for reports to Tanzania’s National AIDS Control Programme (NACP). Clients testing positive for HIV will be linked to care at a local CTC, following NACP guidelines [16]. Invitee testers consenting to become inviters will complete the same enrollment survey as their inviters, which includes a comprehensive HIV risk assessment.

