#### Design of the RCT

The design of the 2-arm RCT is shown in Figure 2. Arm 1 participants will be offered to extend CONSORT invitations or physical invitation cards to any of their network contacts. Arm 2 participants will be offered physical invitation cards alone. Arm 1 represents the intervention arm; Arm 2 represents the active control arm.

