#### Analyses of Secondary Outcomes

##### Acceptability Among Inviters

Logistic regression will be used to model inviters’ decisions to send at least 1 CONSORT invitation. Zero-inflated negative binomial models will model the number of invitations sent as a function of the covariates described above.

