The second premise is that an assurance of confidentiality promotes referrals for HIV testing within social networks. CONSORT is conceptually related to confidential partner notification strategies [40,41], which are known to be highly acceptable to participants [42,43]. The evidence for technology-based notification systems for testing for sexually transmitted diseases, mainly derived from internet-based applications in high-income settings, is mixed: some show success [44-51], while others do not [41,52,53]. The efficacy of an impersonal, confidential approach to accessing network contacts in LMICs has yet to be evaluated. On the one hand, this approach may reduce the cost of contacting partners [54] and circumvent barriers such as nonreciprocal relationships [55], stigma [56], disclosure, and legal risks [57]. On the other hand, a confidential SMS text message is likely to be less motivating than personal communication. This study will compare the acceptability and efficacy of CONSORT versus other means of inviting social network contacts to test for HIV.

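### The Discussion promises a comparison of CONSORT's acceptability with other ways of inviting, but acceptability is defined as SMS use in arm 1 and no comparator is planned

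*Protocol article*

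**What the plan says.** Protocol article, Discussion, Overview (second premise): "This study will compare the acceptability and efficacy of CONSORT versus other means of inviting social network contacts to test for HIV".

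Assessment of Secondary Outcomes: acceptability among inviters will be "described by the percentage of inviters extending at least 1 CONSORT invitation and the average number of CONSORT invitees per inviter". The section then says: "This outcome is assessed only for arm 1 participants".

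Acceptability Among Inviters gives two analyses. The binary one is: "Logistic regression will be used to model inviters’ decisions to send at least 1 CONSORT invitation". The count one is: "Zero-inflated negative binomial models will model the number of invitations sent as a function of the covariates described above". Neither names the study arm or card use as a comparator.

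Design of the RCT: "Arm 1 participants will be offered to extend CONSORT invitations or physical invitation cards to any of their network contacts". Arm 2 is offered cards only.

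Social Network–Based HIV Testing Invitations describes what is asked of every inviter: "Participants will be asked to whom they would prefer to extend an HIV testing invitation through a physical invitation card". Arm 1 can also choose SMS. At the end of the survey, "inviters will be given the respective number of coded invitation cards". Whether cards were handed on is asked by phone after 30 days, and only of inviters who chose cards (Phone-Based Follow-Up Survey; Participant Retention).

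**The concern.** Acceptability is one of the two properties the trial sets out to evaluate, alongside efficacy. Efficacy has a planned comparison between arms. Acceptability has none, although the Discussion names both in the same comparative sentence.

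SMS use in arm 1 answers one question: do inviters choose the SMS option when it is offered? It leaves open whether the option leads them to invite more people. An inviter who sends an SMS to a contact who would otherwise have received a card raises the acceptability measure without adding a contact.

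The distinction also matters for reading the primary result. If more invitees test in arm 1, that could reflect more invitations or more testers per invitation. The planned acceptability analyses do not separate the two.

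**Working it through.** The article gives no expected rate, sample size or power for acceptability, so there is no stated figure to reproduce. The check compares the sections and then asks what a comparison by arm could show.

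**Step 1. Outcome against promise.**

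| Element | Discussion, Overview | Assessment of Secondary Outcomes and Acceptability Among Inviters |
|---|---|---|
| What is measured | acceptability of CONSORT | SMS invitations: any, and mean number |
| Against what | other ways of inviting | nothing |
| In whom | not stated | arm 1 only |

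The count model refers to invitations sent without repeating that these are SMS invitations, so it could be read as covering all types. The outcome definition limits it to CONSORT invitees in arm 1, which makes the narrower reading the likelier one. On either reading, no arm contrast is named.

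**Step 2. What SMS use does and does not identify.** Let S1 be the mean number of SMS invitations per arm 1 inviter, and C1 and C2 the mean numbers of cards issued per inviter in arms 1 and 2. Total invitations are T1 = S1 + C1 and T2 = C2. Then

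S1 = (T1 − T2) + (C2 − C1).

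The planned measure S1 is therefore the sum of the net gain in invitations (T1 − T2) and the cards displaced (C2 − C1). S1 alone cannot separate the two. C1 and C2 can, and both come from the count of cards issued at enrollment.

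**Step 3. Precision of a comparison by arm.** Inputs: 600 inviters (Study Sample) and approximately equal arms (Assignment to Study Arms), so about 300 per arm. The proportion extending at least one invitation is not given, so a range is used. Two-sided 5% is assumed.

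- Planned one-arm description: 1.96 × √(p(1−p)/300) = 3.4 points at p = 10%, 5.2 at 30% and 5.7 at 50%, with no comparator.
- Difference between arms in the proportion extending any invitation: 1.96 × √(2 × 0.5 × 0.5/300) = 8.0 points, which is the maximum. At 70% in both arms: 1.96 × √(2 × 0.7 × 0.3/300) = 7.3 points.
- Detectable increase with 300 per arm (two-sided 5%, pooled variance):

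| Assumed arm 2 proportion | 80% power | 90% power |
|---|---|---|
| 30% | 11.0 points | 12.7 points |
| 50% | 11.4 points | 13.1 points |
| 70% | 9.9 points | 11.4 points |
| 80% | 8.4 points | 9.5 points |

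- By cohort, with about half of each cohort per arm, the increase detectable at 80% power is 10.0 to 13.9 points for HCT inviters (200 per arm) and 13.4 to 19.4 points for CTC inviters (100 per arm).

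The pooled comparison is informative. The CTC comparison alone is coarse.

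**The case against.** The strongest defence is that the restriction to arm 1 is not an error. Arm 2 is never offered CONSORT, so its use can only be observed in arm 1. Arm 1 inviters choose SMS with cards also on offer, so choosing it is in itself evidence of acceptance; whether more people are invited is a separate question about reach. The comparative promise is one sentence in the Discussion. The objective, aims and outcome list speak only of evaluating acceptability. Most of this stands, and it is why SMS use should remain the descriptive measure. It does not remove the mismatch, because the article states a comparison and then fixes an outcome and analyses that do not make one.

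Three stronger readings are tempting, and the article does not support them.

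- **That the comparison is impossible.** It is absent from the outcomes as written, but the enrollment data allow it. Arm 1 choices also permit a non-randomised comparison of SMS with cards.
- **That substitution undermines the trial.** Study Design raises substitution in relation to attributing testing uptake to CONSORT, and deals with it through the card-only arm. The primary outcome counts testers by either route, so substitution nets out there.
- **That a comparison by arm would set SMS against cards head to head.** Arm 1 has both options, so the contrast estimates the effect of adding SMS to cards. The same is true of the efficacy comparison.

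The objection that SMS and cards are unlike units also stands in part. SMS messages are dispatched automatically, whereas an issued card may never be handed on. Self-reported distribution does not repair this: recall and non-response errors would affect all of arm 2's count but only part of arm 1's.

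**Conclusion.** The point holds as a gap between a stated comparison and the outcomes and analyses meant to deliver it. The acceptability measure is not wrong for what it describes, and no primary estimate is biased. What is missing is any analysis showing whether the SMS option increases inviting or only replaces cards.

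A comparison by arm of the proportion extending any invitation would have a 95% half-width of at most 8.0 points. It could detect increases of about 8 to 11 points at 80% power. Both figures rest on about 300 inviters per arm and a two-sided 5% level; the second also rests on assumed arm 2 proportions of 30% to 80%. The article gives no basis for saying how much of the SMS use would be substitution, so no figure is put on that.

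**What to change.** In Assessment of Secondary Outcomes and Acceptability Among Inviters:

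1. Keep SMS use in arm 1 as the descriptive measure of acceptability, and say that the count model for it concerns SMS invitations.
2. Add two secondary outcomes compared by randomised arm, taken from enrollment records: (a) the proportion of inviters extending at least one invitation of any type (SMS selected or card issued), and (b) total invitations per inviter. For (b), state how a contact invited by both routes is counted, since this can arise only in arm 1.
3. Report cards issued per inviter by arm to show displacement, and describe the choice between SMS and card within arm 1.
4. State that the arm contrast estimates the effect of adding the SMS option to cards, and reword the Discussion sentence to match.
5. Use the 30-day self-reported card distribution descriptively only, and note that an issued card is not always handed on.

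The cost is some analysis wording and one more table. No additional participants or data items are needed.
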